## Abstract

**Background:**

Preeclampsia (PE) is a common maternal disease that complicates 5 to 10% of pregnancies and remains as the major cause of maternal and neonatal mortality. Cost-effective interventions aimed at preventing the development of preeclampsia are urgently needed. However, the pathogenesis of PE is not well known. Multiple mechanisms such as oxidative stress, endothelial dysfunction and insulin resistance may contribute to its development. Regular aerobic exercise recovers endothelial function; improves insulin resistance and decreases oxidative stress. Therefore the purpose of this clinical trial is to determine the effect of regular aerobic exercise on endothelial function, on insulin resistance and on pregnancy outcome.

**Methods and design:**

64 pregnant women will be included in a blind, randomized clinical trial, and parallel assignment. The exercise group will do regular aerobic physical exercise: walking (10 minutes), aerobic exercise (30 minutes), stretching (10 minutes) and relaxation exercise (10 minutes) in three sessions per week. Control group will do the activities of daily living (bathing, dressing, eating, and walking) without counselling from a physical therapist.

**Trial registration:**

NCT00741312.

## Background

Preeclampsia is a disease of worldwide distribution, which complicates 5% to 10% of pregnancies and remains as the major cause of maternal and neonatal mortality and morbidity [1,2]. The problem is especially important in developing countries, where maternal mortality ratio is up to twenty fold higher than in developed countries [1]. In Colombia the high incidence of preeclampsia (5.1%), low birth weight (LBW; 13.2%), intrauterine growth restriction (IUGR; 7.9%) and perinatal mortality (3.68 per 1000 live births) is considered a serious public health problem that needs to be solved [3-5]. Multiple conditions such as maternal age, nulliparity, previous personal and family history of PE, poor nutrition, sedentary life styles, residence at high altitudes, and lack of adequate prenatal care have been associated with an increased risk for PE. Multiple mechanisms as oxidative stress, endothelial dysfunction, and insulin resistance, have been proposed to explain the pathogenesis of the disease [6-8]. Changes in the production and in the action of nitric oxide (NO) have been proposed as the key cause of endothelial dysfunction in preeclampsia [9]. Moreover, an increased oxidative stress has been proposed as the main responsible factor for the changes in the vascular reactivity observed during PE [9]. I It was originally proposed that the increased concentration and reactivity to vasoconstrictors observed in PE might be due to a reduction of vasodilator prostaglandins, that results in an imbalance between prostacyclin (PGI_2_) and thromboxane A_2 _(TXA_2_) [10,11]. However, this imbalance in prostaglandins has not been found in early pregnancy in women who subsequently developed PE [10].

Epidemiological evidence suggests that women who participate in programs of regular physical activity have a reduced risk of developing PE [12,13]. Several studies [14-19] have found beneficial effects of maternal physical activity during pregnancy on the delivery, the foetal growth and preterm delivery. Recently, Dempsey et al. [20] reported that physically active pregnant women experienced a 40-70% reduced risk of gestational diabetes as compared with sedentary women. Other investigations have reported that recreational physical activity during pregnancy is associated with a reduced risk of PE [21,22].

Endothelial-dependent vasodilator function can be examined non-invasively in humans by measuring brachial artery mediated dilatation [23,24] and it has been demonstrated that exercise improves flow mediated dilatation (FMD). In normal pregnancy, flow mediated dilatation increases throughout pregnancy[25,26] but the effect of exercise on FMD has not been evaluated in pregnant women.

### Rationale of the study

Evidence supports an inverse association between physical fitness and several risk factors for PE, including glucose intolerance, hypercholesterolemia, high blood pressure, obesity, and markers of systemic inflammation like C-Reactive Protein (CRP). Furthermore, physical fitness may protect against PE by intervening at three key stages of its pathogenesis: 1) Protection against abnormal placental development, 222 2) Reduction of oxidative stress, and 3) Reversal of endothelial dysfunction (Figure 1). To date, only few studies have evaluated the effects of habitual physical activity on endothelial function, and results have been controversial. In addition, no studies assessing the influence of regular aerobic exercise on endothelium-dependent brachial artery flow-mediated dilatation in pregnant women have been published. The present study will be conducted in hope of filling this gap.

**Figure 1 F1:**
[figure not shown]
**Expected benefits of exercise during pregnancy**. Solid-line boxes represent the effects of preeclampsia and endothelial dysfunction. Dashed-line boxes represent the effects of exercise.

## Methods/Design

### Setting

The trial will be conducted at the Universidad del Valle (UV). The Ethics Committee of Fundación Cardiovascular de Colombia (FCV) (Resolution-022/29-UV) approved the trial. All participants will provide written informed consent before entering the study.

### Design and Population

This is a single blind, randomized controlled clinical trial to evaluate the effects of a supervised aerobic exercise program on endothelium-dependent brachial artery flow-mediated dilatation in 64 nulliparous pregnant women. Interested women eligible for the present study will be invited to a pre-test including an interview (Visit A), and assessments at the Hospital Cañaveralejo and Laboratory of Biochemistry of the Universidad del Valle, Cali-Colombia. The first visit will take place between weeks 12 and 20 (Visit B), the second at week 32 (Visit C) and the last one, after delivery (Visit D).

### General objective

To determine the effect of regular aerobic exercise on endothelium-dependent brachial artery flow-mediated dilatation, insulin resistance and pregnancy outcome.

### Specific objectives

1. To determine the influence of aerobic exercise on the functional capacity (VO_2Max_), anthropometry (Fatness, body mass index [BMI]) and biochemical markers (glucose and lipid profile) in the target population.

2. To study the influence of controlled exercise on endothelial function of pregnant women.

3. To evaluate the effect of aerobic exercise on biochemical markers of insulin resistance (HOMA Index).

4. To evaluate the effect of physical exercise on maternal variables (route of delivery, duration of childbirth, postpartum complications) and the newborn (APGAR score and anthropometry).

### Outcome measurements and instruments

The primary outcome is the difference on endothelium-dependent brachial artery flow-mediated dilatation after three months of regular aerobic exercise. [Time Frame: Baseline and 32 weeks gestation]

The secondary outcome measures are High Sensitivity C-Reactive Protein, Nitrates, Nitrites, cyclic cyclic guanosine monophosphate (cGMP), blood lipid profile and glucose, HOMA index, anthropometric indicators, functional capacity (VO_2Max_), [Time Frame: Baseline and 32 weeks gestation] and maternal pregnancy outcomes (type delivery, duration of childbirth, blood pressure evolution, postpartum complications) and newborn outcomes (APGAR score and anthropometry), [Time Frame: Delivery].

### Interventions

#### Exercise Group

Regular aerobic physical exercise: Walking (10 minutes), aerobic exercise (30 minutes), stretching (10 minutes) and relaxation exercise (10 minutes) for 3 months. Exercise will be performed during 3 sessions per week. All sessions will be supervised by a physical therapist and a physical educator. The exercise-program follows the American College of obstetricians and gynecologist (ACOG) [27] and the American college of Sports Medicine (ACSM] exercise prescription [28]. Aerobic activities will be performed at moderate intensity (60-70% of maximal heart rate) measured by the 6-20 Borg's rating scale (PER). Each session will start with a 5 minutes warm up, followed by 30 minutes of aerobic activity, including a 5 minutes cool down. This is followed by 15 minutes of exercises circuit strength training of the upper limbs, lower limbs, and deep abdominal muscles stabilization. The last 5 minutesconsist of stretching and relaxation exercises.

#### Control Group

Activities of daily living: basic activities of daily living (bathing, dressing, eating, walking) without counselling from a physical therapist but including 6 sessions of prenatal behaviour control during a month [28]. *Appendix 1*.

#### Sample size

FMD is a measure of endothelial function validated in several population studies, taken as the critical variable to calculate the sample size. A sample size of 64 subjects was estimated. The sample size was calculated assuming a specific difference between the groups of 4% in the FMD after 3 months of treatment; with a maximum standard deviation of 4.5. It was accepted a type I error of 0.05, a power of 80%, and it was adjusted by 20% [29].

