#### Randomization

Pregnant women who satisfy eligibility criteria will be randomized into one of two groups: 1) aerobic exercise group (controlled by a physical therapist and a nurse, and 2) usual prenatal control. Randomization will be performed using a variable blocking desing with a permuted block of maximum 8 subjects. Exercise will start only when each block is completed; because it consists of supervised sessions in groups of 3 to 5 women. Randomization will be administrated only by the coordinator of study, who is not involved in the intervention or in the measuring of clinical parameters. Given the nature of the interventions, it is not possible to blind the participating individuals. Instead, a research assistant at each site will control all the primary and secondary outcome assessments in order to blind to treatment assigned. While no specific qualifications or experience are required of the research assistants, training will be provided prior to the initiation of the trial about protocol and measurement procedures and methods used to maintain the blind. These procedures are also detailed in the study operations manual. Moreover, the importance of maintaining the blinding and allocation concealment will be reinforced by regularly scheduled conference calls at the sites and daily meetings with the camp investigators. Figure 2.

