#### Statistical Analysis

There will be an exploratory analysis which will include mean values and standard deviations of each of the variables studied to determine the balance at baseline between the groups. Normality of distribution will be checked for all variables using the Kolmogorov-Smirnov test.

The primary outcome will be the differences on endothelium-dependent brachial artery flow-mediated dilatation between the groups; and the secondary outcomes will be the differences related to anthropometric, functional and metabolic parameters, and pregnancy outcomes. The comparison between the groups will be made after treatment using the student t test for those variables with normal distribution and the non parametric Mann-Whitney test for those with non-normal distribution. Then, a linear regression analysis will be performed to determine the effect for each variable on the FMD, modeling it with Greenland parameters to determine which variable has a relationship with the model. Statistical analyses will be carried out using the SPSS software (version 14.0, SPSS, Chicago, IL). A p value < 0.05 will be considered statistically significant.

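### The total of 64 women does not follow from the sample-size calculation as described, which gives 48 to 54

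*Protocol article*

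**What the plan says.** The Sample size section takes FMD as the variable that sets the size of the trial. It states the result ("A sample size of 64 subjects was estimated") and then its inputs: "a specific difference between the groups of 4% in the FMD after 3 months of treatment", "with a maximum standard deviation of 4.5", and "It was accepted a type I error of 0.05, a power of 80%, and it was adjusted by 20" (the last figure is a percentage). The total of 64 is repeated in the Abstract, under Design and Population and under Eligibility, so it is not a slip in one place.

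The section does not say whether the test is one- or two-sided, how many women per group were needed before adjustment, what the 20% is for, or how it was applied. Elsewhere the article says that women "will be randomized into one of two groups", without a ratio. Under Statistical Analysis it plans the "student t test for those variables with normal distribution and the non parametric Mann-Whitney test for those with non-normal distribution", and adds: "A p value < 0.05 will be considered statistically significant".

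**The concern.** The article prints every input of a standard comparison of two means and then a total that those inputs do not produce. The gap is too large to be rounding. This section is the only place that states the effect the trial was sized to detect on its primary outcome. A reader who has to interpret a null FMD result would take from it that the trial had 80% power for 4 points after allowing for 20%. If the printed difference and SD are right, the trial has more power than that. If the SD or the difference actually used was another figure, then the assumed variability or the target effect is misreported. The text does not let the reader tell these cases apart.

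**Working it through.** **Inputs from the Sample size section.** Difference 4 (read as absolute FMD percentage points), SD 4.5, alpha 0.05, power 80%, adjustment 20%.

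**Assumed.** Two-sided test, 1:1 allocation, and 4.5 as the SD of the outcome being compared.

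**Step 1: number per group before adjustment.**
n = 2 × (1.96 + 0.8416)² × (4.5/4)² = 2 × 7.849 × 1.2656 = 19.87, so 20 per group. The same calculation with the noncentral t distribution gives 20.87, so 21 per group.

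**Step 2: one 20% adjustment, in each of its two usual forms.**

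| Method | n per group | × 1.2 | Total | ÷ 0.8 | Total |
|---|---|---|---|---|---|
| Normal | 20 | 24 | 48 | 25 | 50 |
| t test | 21 | 25.2, so 26 | 52 | 26.25, so 27 | 54 |

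The stated 64 is not reproduced. The excess is 64 − 54 = 10 women (10/54 = 19%) to 64 − 48 = 16 women (16/48 = 33%). A one-sided test moves further away, to between 40 and 44.

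**Step 3: what 64 delivers at the stated difference and SD.**
- 32 per group: 4 / (4.5 × √(2/32)) = 3.556, and 3.556 − 1.96 = 1.596, so power is 94.5% by the normal approximation and 93.8% by the t test.
- After 20% loss, 32 × 0.8 = 25.6 per group: t-test power 87.6%. With a whole number of 25 per group it is 86.8% by the t test and 88.2% by the normal approximation.
- Difference detectable with 80% power at 25.6 per group (t test): 3.59, about 3.6 points.

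**Step 4: routes that do reach 64.** None is described in the article.

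With every stated input unchanged:
- 20% applied twice: 20 / (0.8 × 0.8) = 31.25, so 32 per group. This needs the normal-approximation figure; starting from 21 it gives 66 in total.
- A Mann-Whitney allowance, then 20% loss: 21 / 0.864 = 24.3, so 25; 25 / 0.8 = 31.25, so 32 per group.

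With one input changed:
- Power 90%, normal approximation, unrounded: 26.60 × 1.2 = 31.92, so 32 per group.
- SD 5.0: 25 per group; 25 / 0.8 = 31.25, so 32.
- Difference 3.5: 26 per group; 26 × 1.2 = 31.2, so 32.
- Alpha 0.025: 25 per group; 25 / 0.8 = 31.25, so 32.

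**The case against.** Three objections deserve an answer.

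First, a reader might infer that the stated power, or some other stated input, must be wrong. The document does not support that. It says only that there was a 20% adjustment, and Step 4 shows two ways of reaching 64 with every stated input intact. Neither is a natural reading: the first inflates 20 per group by 56% (1/0.64 = 1.5625), and the second adds an allowance that the section never mentions, for a test that Statistical Analysis names only for non-normal variables. But they are enough to show that a misreported input is not the only explanation. This objection stands.

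Second, a reader might infer that 90% was the real planning power, because it gives 64. That match is fragile. It holds only for the normal approximation, unrounded, multiplied by 1.2. Rounding first gives 27 × 1.2 = 32.4, so 33 per group and 66 in total; the t test or division by 0.8 gives 68 to 70. The article nowhere mentions 90%, and several other single changes reach 64 as well. This objection also stands.

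Third, the article is condensed and cites a source for the calculation, so the formula and the basis of the 20% may be set out elsewhere. That excuses missing detail, but it does not remove the point. The article prints its inputs and its result, and under the usual formulas the two disagree.

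**Conclusion.** The point holds in limited form. With a two-sided test, 1:1 allocation and a single 20% adjustment, the printed inputs give 48 to 54 women, and 64 is 10 to 16 more. Either an input or the account of the adjustment is wrong or incomplete, and the document does not settle which.

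The error is on the safe side. Nobody should read it as a sign that the trial is too small: on its own difference and SD it has about 94% power with full retention and about 87% to 88% after 20% loss. Nor does the article claim that 4 points is the smallest detectable difference; the figure of about 3.6 points is information for the reader, not a correction of a stated claim. What is at stake is the accuracy of the planning statement for the primary outcome. It should be corrected, but it does not threaten the validity of the trial.

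**What to change.** Keep 64 and correct the Sample size statement from the sponsor's records of the calculation:

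- State the sidedness of the test, the number per group before adjustment, what the 20% allows for, and how it was applied.
- If the SD, difference, alpha or power actually used differs from the printed one, correct that figure.
- If the other inputs stand and no further allowance was made, replace 80% with what 64 delivers: about 94% power with 32 per group, about 87% to 88% after 20% loss, and a difference of about 3.6 points detectable with 80% power after that loss.
- Do not insert 90% unless the sponsor confirms that it was the planning value. If it is confirmed, show the unrounded step (26.6 × 1.2 = 31.9, so 32 per group), because 27 × 1.2 does not give 32.

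The cost is one or two sentences of wording. Enrolment and analysis do not change.

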#### Eligibility

64 pregnant nulliparous women, healthy, 16 to 30 years old. *Appendix 2*.

#### Randomization

Pregnant women who satisfy eligibility criteria will be randomized into one of two groups: 1) aerobic exercise group (controlled by a physical therapist and a nurse, and 2) usual prenatal control. Randomization will be performed using a variable blocking desing with a permuted block of maximum 8 subjects. Exercise will start only when each block is completed; because it consists of supervised sessions in groups of 3 to 5 women. Randomization will be administrated only by the coordinator of study, who is not involved in the intervention or in the measuring of clinical parameters. Given the nature of the interventions, it is not possible to blind the participating individuals. Instead, a research assistant at each site will control all the primary and secondary outcome assessments in order to blind to treatment assigned. While no specific qualifications or experience are required of the research assistants, training will be provided prior to the initiation of the trial about protocol and measurement procedures and methods used to maintain the blind. These procedures are also detailed in the study operations manual. Moreover, the importance of maintaining the blinding and allocation concealment will be reinforced by regularly scheduled conference calls at the sites and daily meetings with the camp investigators. Figure 2.

**Figure 2 F2:**
[figure not shown]
**Study design**.

### Procedures

#### Enrollment

This study will be performed in pregnant women with an anticipated enrollment period of 12 months. Screening of participants will consist in the evaluation of inclusion and exclusion criteria, explanation of the study protocol, and the assessment of the willingness to participate in the study. Eligible subjects will be scheduled to the following visits:

**- Visit A: **to perform a structured validated interview (socio-demographic data, habits, medical record) and a detailed physical examination. Prenatal care visits will be continued in the primary care center assigned as part of her health insurance plan.

#### Baseline assessments and active follow-up

**- Visit B: **will include measurements of blood pressure, anthropometric parameters, FMD, functional capacity (VO_2Max_) and electrocardiogram. A fasting blood sample will be obtained to determine glucose and insulin levels, lipid profile, high sensitivity C - reactive protein (hs-CRP), nitrates, nitrites, cGMP. During this visit participants will be randomized to one of the two groups. For this purpose, a randomization system using maximum blocks of 8 will be used.

**- Visit C: **At 32 week gestation repeating measurements described above.

- **Visit D: **the following pregnancy outcomes will be recorded post partum: pregnancy duration, blood pressure evolution, characteristics of childbirth (route and duration of childbirth, postpartum hemorrhage), newborn outcomes (gestational age at birth, Apgar score, weight, height, head circumference and abdominal circumference in cm). With these measures variables will be constructed: (weight/height^3^), head circumference/birth weight and weight/height indexes [30]. In addition, the number of prenatal controls and information regarding pregnancy complications will be registered.

#### Passive follow-up

All the women included in the study will undergo a passive follow-up post delivery control 30 days after delivery (by phone).

#### Blood samples

In fasting conditions (at least 10 hours), blood samples will be withdrawn from the antecubital vein, with appropriate conditions of asepsis and antisepsis, using 3 vacutainer tubes, one dry, another with citrate, and the other containing EDTA. After 10 minutes in vertical position, all samples will be centrifuged at 3000 rpm during 15 minutes to extract the serum or plasma. Part of the samples obtained during visits B and C will be stored in Eppendorf vials at -70°C until the end of the study.

#### Physical measurements

Anthropometric will be performed in each participant at enrollment and before delivery. Standard measurements will be performed in duplicate by the same examiner on each woman. All determinations will be realized in fasting patients, wearing light clothes and without shoes, using standardized formats and methods [31].

**Weight**: will be measured with the patient standing and then registered after rounding it to the nearest 200 grams. The weight scale will be calibrated to 0 before each measurement.

**Height**: will be measured using a metric tape with the patient standing against the wall in Frankfort's position, and the value marked by a ruler placed horizontally on the head of the patient.

**Heart rate**: number of beats per minute will be measured in the radial artery.

**Blood pressure**: will be taken twice (with a difference of 5 minutes between the measurements) using a mercury sphygmomanometer on the right arm, with the patient comfortably seated, after a 5 minute rest. Systolic blood pressure (SBP) will be determined by the first audible sound (Korotkoff phase 1). Diastolic blood pressure (DBP) will be registered when the sound disappears (Korotkoff phase 5) [32]. The patient should not have smoked 30 minutes prior to the blood pressure measurement. The pneumatic arm cuff must cover 2/3 of the upper arm's length; its inferior border must be 2-3 cm over the antecubital space; the cuff will be slowly deflated. The mean blood pressure (MBP), will be calculated using the following formula [SBP+(2*DBP)]/3.

**Body composition: **% fat mass indirect (FM; kg), fat-free soft tissue mass (FFT; kg), will be measured at baseline and follow-up visits using indirect formulas [33].

**Body Mass Index (BMI)**: This index will be estimated using the weight in kilograms divided by the second power of the height expressed in meters.

